### Primary Outcome

The primary outcome is change in the proportion of prehospital stroke system patients with suspected LVO who are treated with mechanical thrombectomy before and after implementation of TCC Coordinated SBST. We hypothesize that compared to standard triage, TCC Coordinated SBST will be associated with a significant increase in the proportion of patients encountered by EMS with suspected LVO who are treated with MT.

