### Mixed Methods Multi-Phase Design

A recent prehospital stroke system of care consensus conference advised collaboration of regional stakeholders to create an optimally adapted prehospital stroke system (23). A mixed methods methodological approach which aims to integrate rigorous quantitative and qualitative methods within a study will be the most effective way to understand varied and multi-level stakeholder perceptions and optimize implementation of this complex health intervention across different service contexts (24). We will use a multi-phase QUAL+QUAN → QUAN → QUAL mixed methods design to assess stakeholders' views about the implementation process capitalizing on the advantages of integrating quantitative and qualitative methods using surveys and quantitative measures, focus groups and individual semi-structured interviews (24–27). We will use quantitative and qualitative methods to aid in the development of context specific forms of the model prior to implementation (28–30). Quantitative data will include patient-specific factors (EMSA score, Alert, responds to Voice, responds to Pain and Unresponsive scale, time last known well, potential tPA eligibility, vital signs), EMS factors (EMS air and ground resources, estimated travel times to nearest available non-MTC and MTC), and hospital factors (stroke center level, imaging, and treatment capabilities, location). Qualitative data consisting of focus groups and interviews with stakeholders will be critical for development of regional triage plans and stroke center protocols. An example Focus Group Guide for the TCC paramedic communicators is available (Supplementary Material 1). After implementation, we will survey stakeholders to assess perceptions of feasibility, appropriateness, and acceptability of the intervention and employ follow-up qualitative interviews with purposefully selected individuals to understand context-specific barriers and facilitators more fully to intervention adoption, implementation, maintenance, and spread. Systematic integration and triangulation of quantitative and qualitative data will assure more valid conclusions (31).

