### Patient Population—Inclusion and Exclusion Criteria

The study will include patients entered in the Alabama stroke system by EMS with suspected LVO based on an EMSA ≥ 4 with one point scored for each abnormal response on the 6-item scale. The study will exclude patients with stroke onset while hospitalized, a time last known well ≥24 h prior to initial EMS contact, and patients who only respond to pain or who are unresponsive based on the Alert, responds to Voice, responds to Pain and Unresponsive Scale (19). The flow of patients during the study is shown in Figure 3.

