**Figure 3 F3:**
[figure not shown]
Flow of patients during study. The study will include prehospital patients entered into the stroke system by EMS with an EMSA ≥ 4. Patients with a time last known well (LKW) > 24 h or those who respond only to pain or who are unresponsive will be excluded. During the standard triage period, patients meeting study entry criteria will be transported to the closest stroke center with capacity. During TCC Coordinated SBST, patients will be routed by TCC directly to a MTC (including comprehensive stroke centers and thrombectomy-capable primary stroke centers) if additional transport time complies with region-specific transport time limits and will not preclude use of tPA. Otherwise, TCC will coordinate transport to the closest stroke center of any level and initiate a region and hospital specific plan to expedite inter-facility transfer to a MTC for appropriate patients.

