(1) EMS Training in the EMSA: As previously noted, our model was designed to address barriers to prehospital stroke care (16, 17), by focusing training, experience, and feedback on the TCC paramedic communicators. However, we applied what we have learned from our preliminary study to enhance our training program for EMS providers in the field (15). For example, we included explicit strategies in the EMSA to enable determination of abnormal horizontal gaze or lateralized weakness of the face, arm, or leg in confused or aphasic patients. The training program was also informed by prior qualitative studies on paramedic decision-making for high acuity patients (mostly trauma) that have found a reliance on the paramedic's initial “gut” impression (33) and a study that found that the diversity of stroke presentations was a barrier to acute stroke recognition by paramedics (34). We addressed these issues by providing “snapshot” figures representing left and right middle cerebral artery syndromes in addition to training on individual scale items to aid EMS providers who favor a gestalt approach to diagnosis. We created two training videos for presentation at regional zoom kick-off events including EMS agencies and hospitals. A 24 min video, “Severity-Based Stroke Triage: Key Concepts,” covers the State's plan for roll-out of severity-based stroke triage, stroke vs. stroke mimics, large vessel occlusion, the EMSA, treatment options for acute ischemic stroke, and the concept of time last known well (35). The other video is a 9 min demonstration of the “Emergency Medical Stroke Assessment” by paramedics (36). After the regional kick-off events, paramedics across the state were required to view the training videos and complete a 20 question post-training examination. The EMS training videos and examination take <90 min to complete.(2) EMS stroke severity assessment and prenotification: After statewide EMSA training is complete, TCC Guided EMSA with item-specific prenotification and focused feedback will be expanded to all EMS regions in Alabama. Key elements from the preliminary study that have been incorporated into the current protocol include TCC guidance of EMS performance of the EMSA when needed, item-specific prenotification by TCC rather than a summary score, and ongoing review of recorded interactions between TCC and EMS with feedback to TCC to enhance their guidance skills (15). During the standard triage data collection period in each EMS region, all stroke patients (including those with suspected LVO based on an EMSA ≥ 4) will undergo triage to the nearest stroke center with capacity of any level (Figure 3). Additional training for TCC will be employed as needed to optimize performance of the TCC Guided EMSA.(3) Prehospital Severity-Based Stroke Triage: Plans will be developed during the standard triage period in each region considering EMS and hospital resources, levels and numbers of stroke centers, travel times by ground and air in each region, and data from focus groups and interviews. A schematic of the flow of patients within each EMS region during SBST implementation is shown in Figure 3. During implementation, patients entered into the stroke system by EMS who have an EMSA ≥ 4 with a time last known well ≤ 24 h who are alert or respond to voice will be triaged as follows: If direct transport to a MTC (including comprehensive stroke centers and thrombectomy-capable primary stroke centers) complies with region-specific transport time limits and will not preclude use of tPA, TCC will coordinate pre-notification and air or ground transport to a MTC. If direct transport time to a MTC is greater than region-specific limits or transport to a MTC will preclude use of tPA, TCC will coordinate pre-notification and air or ground transport to the closest available stroke center of any level and initiate a region and hospital specific plan to expedite inter-facility transfer to a MTC.(4) Emergency Department Severity-Based Stroke Triage: The implementation strategy includes an educational conference to be held in each region to review regional implementation plans, foster engagement of stroke center personnel and EMS, provide a “toolkit” of resources to streamline care, and train stroke coordinators throughout Alabama. The grant supports reimbursement for stroke coordinators who successfully pass the Stroke Certified Registered Nurse examination offered American Board of Neuroscience Nursing (37). The plan includes interviews and focus groups with stroke center directors and coordinators, on-site evaluation if possible, protocol development, and training on stroke treatment options and the EMSA. We will encourage EMSA performance systematically as part of code strokes on patient arrival. Depending on available resources, context specific forms might include multimodal computerized tomography (CT) including noncontrast CT, CT angiography, and CT perfusion on code stroke patients with suspected LVO, telestroke or image sharing with MTCs, and transitioning from alteplase to tenecteplase to facilitate rapid treatment and transfer.(5) Inter-facility Severity-Based Stroke Triage: Plans for secondary triage will be developed during the standard triage period and will depend on regional resources as well as data from focus groups and interviews. The plan includes TCC monitoring of the status of patients with suspected LVO who are initially transported to non-MTCs, modeled after the TCC Trauma system process. In this process, the TCC follows up with the ED every 20 min to update patient status and identify the best options for secondary triage in real-time. Context specific strategies might include holding the EMS unit involved with primary triage of patients with suspected LVO at the non-MTC until a transfer decision is made or tPA is initiated, modeled after the Alabama Trauma system “Rescue Stop.” Alternatively, TCC might proactively mobilize ground or air resources to achieve rapid patient transfer.

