### Sample Size Estimates for Stepped Wedge Cluster Trial

Based on 2018 data, the Alabama stroke system volume is about 7,630 over a 1-year period. Based on our pilot data (15), we estimate exclusion of 10% (763 patients) who are unresponsive or poorly responsive, and 5% (382 patients) with time last known well >24 h. We will allow for 10% missing EMSA data (763 patients), leaving 5,722 patients. Pilot data also indicate that over 1 year ~41% of this population (2,346 patients) will have EMSA ≥ 4 and be eligible for enrollment, 18% of enrolled patients (423 patients) will have LVO and be available for analysis of our primary endpoint, and ~50% of the patients with LVO are treated with MT (211 patients). Thus, for our power analyses, we will use 50% as the reference to examine whether implementation of TCC Coordinated SBST will be associated with a significant increase in the proportion of stroke system patients with suspected LVO who are treated with MT. Because of the Before-After nature of the data, a test that accounts for this dependency is necessary. However, even though these are repeated observations the dependency could be rather weak. Many of the same entities (e.g., hospitals, doctors, and paramedics) will be involve both before and after, the patients are very likely to be different; thus, leading to weaker dependency. To account for this possibility, we varied the strength of the dependency (correlation) from *r* = 0 to 0.5. Because the effect of implementing TCC Coordinated SBST is unknown, we varied the effect from small 10% to large 40% improvement. For a weak dependency of (*r* = 0.1), we would need ~350 subjects before and after to detect a moderate 20% improvement with 80% power at a α = 0.05 significance level. This corresponds to an increase of 35 patients treated with MT after TCC Coordinated SBST implementation. A smaller 15% improvement (increase of 26 patients treated with MT) with stronger dependency (*r* = 0.5) would also require ~350 subjects before and after to obtain 80% power at a α = 0.05 significance level. In either case, this data could be collected in ~20 months. Our sample size estimates are based on statewide stroke system entry volume data. Estimates of study eligibility volume and LVO frequency are based on methodology used in our preliminary study. However, to account for the possibility of smaller stroke system volume, smaller effect size, and/or weaker dependency, we plan on 36 months of data collection. For the proposed 36-month data collection timeline, with potentially 1,200–1,300 total observations, we should have more than adequate statistical power to detect a 15% improvement in the primary endpoint even with a weak dependency (*r* = 0.1) among observations.

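### The pooled statewide contrast is a valid primary estimand but dilutes any routing effect, and Table 3's related row conditions on a destination that SBST itself changes; nearest-center type is the better stratum

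*Protocol article*

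**What the plan says.** The Primary Outcome section defines the endpoint as the "change in the proportion of prehospital stroke system patients with suspected LVO who are treated with mechanical thrombectomy before and after implementation" of SBST. Eligibility rests on the prehospital score and has no criterion on which center is nearest: "The study will include patients entered in the Alabama stroke system by EMS with suspected LVO based on an EMSA ≥ 4".

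The two periods differ in destination. Under standard triage (Figure 3 legend), "patients meeting study entry criteria will be transported to the closest stroke center with capacity", and Intervention item (2) says that all stroke patients "will undergo triage to the nearest stroke center with capacity of any level". Under SBST, "patients will be routed by TCC directly to a MTC" when the region's time limits and tPA timing allow it, and otherwise to the closest center.

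The Statistical Analysis section names mixed models and estimating equations for the binary endpoint, with no term for nearest-center type. Table 3 lists, under Effectiveness, a differential-effectiveness row for patients whose initial triage was to a non-MTC. The Mixed Methods Multi-Phase Design section lists "estimated travel times to nearest available non-MTC and MTC" among the EMS factors considered when context-specific triage forms are developed.

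**The concern.** A patient whose closest available center is an MTC goes to the same place first in both periods. Seven in-state MTCs are named, in regions 1, 3, 5 and 6, so such patients exist. Re-routing can act only on the others, and the pooled contrast averages the two groups.

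Two things are at stake. First, a modest pooled result could mean a weak routing effect everywhere or a strong one in the minority who can be re-routed, and no planned analysis cleanly separates these readings. Second, the Table 3 row that comes closest to doing so is defined by where the patient was actually taken. SBST exists to change that, so the row compares differently selected patients before and after.

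**Working it through.** **1. The plan's own sample size.** Inputs come from the Sample Size section: a reference MT rate of 50% ("we will use 50% as the reference"), improvements read as relative (20% gives 60%, 15% gives 57.5%), 80% power and α = 0.05. Sidedness is not stated; two-sided is assumed. With correlation r,

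n per period = (1.96 + 0.842)² × V / (p2 − p1)², where V = p1q1 + p2q2 − 2r√(p1q1p2q2).

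- 50% to 60%, r = 0.1: n = 346 (plan: about 350)
- 50% to 57.5%, r = 0.5: n = 345 (plan: about 350)
- 50% to 57.5%, r = 0.1: V = 0.4449, n = 621, total 1,242 (plan: 1,200–1,300)

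The plan's figures reproduce. Its effect is set on the pooled scale, so this arithmetic is not wrong.

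**2. Dilution.** Let f be the share of patients whose nearest available center is an MTC, and d the gain in the rest. If MTC-nearest patients gain nothing, the pooled gain is (1 − f)d. The protocol does not give f; 20% to 60% is an assumption. Further assumptions are a 50% baseline in both strata, no clustering or time terms, r = 0.1 and 625 per period. Power = Φ(effect/√(V/n) − 1.96), with n = 625 pooled and 625(1 − f) in the stratum.

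Worked case, f = 40%, d = 7.5 points:
- Pooled: gain 4.5 points, V = 0.4482, SE = √(0.4482/625) = 0.0268, power = Φ(1.68 − 1.96) = 39%.
- Stratum: n = 375, V = 0.4449, SE = 0.0344, power = Φ(2.18 − 1.96) = 59%.

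| f | pooled gain (points) | pooled power | non-MTC-nearest stratum | difference between strata |
|---|---|---|---|---|
| 0% | 7.5 | 80% | 80% | – |
| 20% | 6.0 | 61% | 71% | 20% |
| 30% | 5.25 | 50% | 65% | 25% |
| 40% | 4.5 | 39% | 59% | 28% |
| 50% | 3.75 | 29% | 51% | 29% |
| 60% | 3.0 | 20% | 43% | 28% |

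The last column is the power to show that the two strata change differently, using SE = √(0.445 × [1/(625(1 − f)) + 1/(625f)]).

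With d = 10 points, pooled power is 85% to 32% and stratum power 92% to 66% over the same f.

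Seen the other way, a pooled gain of 7.5 points needs 7.5/(1 − f) in the stratum: 9.4 points at f = 20%, 12.5 at 40%, 18.8 at 60%.

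These figures use the base of the Sample Size section ("18% of enrolled patients (423 patients) will have LVO and be available for analysis of our primary endpoint"), which is narrower than the suspected-LVO population in the Primary Outcome section. The factor 1 − f has the same form on either base.

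**3. Selection in the Table 3 row.** Before implementation, patients first taken to a non-MTC are all those nearest a non-MTC. Afterwards they are mainly those whom the time limits or tPA timing kept from being re-routed. Illustration with assumed figures: half the non-MTC-nearest patients are re-routable with a 50% MT rate, and half are not, with a 40% rate. Before: 0.5 × 50% + 0.5 × 40% = 45%. After, with no effect in anyone who stays: 40%. The row shows a 5-point fall that is pure selection. With the two rates swapped it would show a 5-point gain (45% to 50%). Nearest-center type, set by pickup location, largely avoids this.

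**The case against.** The best defense is that the protocol evaluates a statewide policy for its broad public health impact, so the statewide average is the quantity it means to estimate, and that interaction terms and subgroups are normally left to the analysis plan. Both points stand. Pooling is not a bias, and a missing covariate in a protocol article is not an error. What remains is that the article does fix one related analysis, the Table 3 row, and fixes it on a variable that the intervention changes. The staggered roll-out also already gives a comparison over time, so a second trend check is a supplement.

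A reader might infer that the primary test is underpowered or should be replaced. The documents do not support this: f is unknown, the planned effect is on the pooled scale, and adding a stratum leaves the power of the primary test unchanged.

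A reader might also infer that MTC-nearest patients form a clean negative control, so that an equal change in them would disprove an SBST effect. That fails too. Regional conferences, coordinator training and score use on arrival (Intervention, item 4), and several optional ED measures in Table 2, are not confined to non-MTCs. The Secondary Outcomes section names MTC overload as a possible consequence of the intervention. No MTC is named in regions 2 and 4, so the comparison may not exist there. Its power is also only 20% to 29% in the case worked above.

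Finally, nearest-available status depends on capacity, which hospitals update continually, and a thrombectomy-capable designation is being added. Defined by availability, the stratum could itself shift between periods.

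**Conclusion.** The point holds as an improvement to a supporting analysis. The statewide contrast should stay primary. It averages in patients whose first destination SBST cannot change, which scales any routing effect by 1 − f. The size is unknown because f is not given. For a 7.5-point effect confined to re-routable patients, pooled power runs from about 61% to 20%, against 71% to 43% in the non-MTC-nearest stratum, for f from 20% to 60%. This rests on no effect in MTC-nearest patients, equal baselines, r = 0.1, 625 per period and no clustering. The firmer part needs no value of f: on its plain reading, Table 3's destination-based row compares differently selected groups before and after and cannot be read as an SBST effect.

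**What to change.** 1. For every patient in both periods, derive whether the nearest stroke center is an MTC, from pickup location and a list of centers and their MTC status fixed in advance. Use availability at the time of the call as a sensitivity definition.
2. In the Statistical Analysis section, add this variable and its interaction with SBST as a prespecified supporting analysis, and keep the pooled contrast as primary.
3. Report the SBST effect in non-MTC-nearest patients, replacing or accompanying the destination-based row in Table 3.
4. Report the before/after change in MTC-nearest patients descriptively as an imperfect check on secular trend. Note that non-routing components and MTC overload can affect it and that it may be unavailable in regions 2 and 4. Attach no decision rule to it.

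The cost is one derived variable and some analysis text, with no new patients. Per-patient capture in both periods must be confirmed: travel times are listed as an input to developing triage forms, but the Data Management section does not name them as a study variable, and the data collection forms are not shown. The interaction test will have low power and should be presented with its interval.

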### Secondary Outcomes

Consistent with the aims of implementation research, in addition to effectiveness, we seek to fully assess change in the broad public health impact before and after implementation of TCC Coordinated SBST using the RE-AIM (Reach, Effectiveness, Adoption, Implementation, and Maintenance) framework (AIM 2) (38, 39). The public health outcomes of TCC Coordinated SBST across RE-AIM dimensions are shown in Table 3. There may be unintended negative consequences to implementation of TCC Coordinated SBST, including delay in access to tPA and longer EMS response times. We address these concerns by explicitly tracking the impact of the intervention on these outcomes (see Table 3). Another concern is overloading MTCs with patients without LVO due to false positive screens and reducing capacity of MTCs to accept transfers of patients for MT. In part, we are hoping to mitigate against this by adding a designation in Alabama for thrombectomy-capable primary stroke centers. We will also track the proportion of LVO patients requiring inter-facility transfer, the timeliness of transfer, and rate of MT among all confirmed LVO strokes for patients entered into the Alabama Stroke System (see Table 3). As part of the stepped wedge trial, we will collect data on the rate of true positive and false positive LVO screens. Because statewide stroke system data collection will include whether an LVO was confirmed, LVO location, and whether the patient received MT, we will be able to determine the rate of true negative and false negative LVO screens, and accordingly, sensitivity and specificity of prehospital LVO screening.

**Table 3 T3:** RE-AIM framework to evaluate the public health impact of TCC Coordinated SBST.

**RE-AIM dimension**	**Outcomes**	**Data source**
**Reach**	• Proportion of Alabama MT patients who undergo TCC Coordinated SBST	• ADPH RESCUE ePCR and LifeTrac database
	• Differential reach by race, ethnicity, sex, and population density	• ADPH RESCUE ePCR and LifeTrac database
**Effectiveness**	• Proportion and timeliness of MT for EMS-suspected LVO	• LifeTrac and ADPH REDCap databases
	• Proportion and timeliness of MT for all confirmed Stroke System LVO	• LifeTrac and ADPH REDCap databases
	• Proportion and timeliness of tPA treatment	• LifeTrac and ADPH REDCap databases
	• Proportion requiring inter-facility transfer and timeliness of transfer	• LifeTrac and ADPH REDCap databases
	• Differential effectiveness by race, ethnicity, sex, and population density	• LifeTrac and ADPH REDCap databases
	• Differential effectiveness for patients initially triaged to a non-MTC	• LifeTrac and ADPH REDCap databases
	• modified Rankin Scale 3 months after discharge	• ADPH REDCap databases
	• County/Regional EMS response times	• ADPH RESCUE ePCR
**Adoption**	• Proportion of Alabama EMS organizations that participate	• ADPH RESCUE ePCR and LifeTrac database
	• Proportion of stroke centers participating	• ADPH RESCUE ePCR
**Implementation**	• Proportion of stroke system patients with TCC-guided EMSA performed by EMS	• LifeTrac database
	• Proportion of EMS transports triaged past a non-MTC to a MTC when advised	• LifeTrac database
	• TCC and stroke center adherence to the region-specific triage plan	• LifeTrac and ADPH REDCap databases
	• Differential implementation for rural vs. urban populations	• LifeTrac and ADPH REDCap databases
**Maintenance**	• Sustained adoption and implementation over time	• LifeTrac and ADPH REDCap databases

*RE-AIM, Reach, Effectiveness, Adoption, Implementation, and Maintenance; TCC, Trauma Communications Center; SBST, Severity-Based Stroke Triage; ADPH, Alabama Department of Public Health; RESCUE ePCR, Recording of Emergency Medical Services Calls and Urgent-care Environment electronic Patient Care Reports; LVO, Large Vessel Occlusion; MT, Mechanical Thrombectomy; EMS, Emergency Medical Service; tPA, tissue Plasminogen Activator; MTC, Mechanical Thrombectomy Center*.

After implementation, we will use validated, quantitative surveys of stakeholders to assess perceptions of feasibility, appropriateness, and acceptability of the intervention (40). We will employ follow-up qualitative interviews with purposefully selected individuals to identify barriers and facilitators to adoption, implementation, maintenance, and spread using a mixed methods approach (AIM 3). This will help identify context-specific strategies to guide implementation efforts elsewhere.

